## Abstract

**Introduction:** Dry eye disease (DED) is a very frequently encountered ocular disease, making it a growing public health burden. However, current treatments for DED present unmet medical needs owing to their side effects or ineffectiveness. Therefore, an effective and safe therapeutic agent to manage DED is needed. **Method and Analysis:** We planned a phase 2, dose-finding, double-blind, randomized placebo-controlled trial to evaluate the efficacy and safety of two different doses of USL (Useul), the extract of Achyranthis Radix, compared with placebo, for DED. USL has been found to protect against DED by inducing tear secretion and improving corneal irregularity via anti-inflammatory effects, which will provide new therapeutic options. One hundred and twenty participants will be enrolled, after assessing the inclusion/exclusion criteria, at Daejeon University Daejeon Korean Medicine Hospital. Enrolled participants will be allocated to standard-dose USL, high-dose USL, or placebo groups in a 1:1:1 ratio and will be required to administer the trial medication twice a day for 12 weeks and visit the clinic five times. For efficacy outcomes, objective endpoints of fluorescein corneal staining score, tear break-up time, Schirmer’s test, and meibomian test and subjective endpoints of Ocular Surface Disease Index, visual analog scale, Standard Patient Evaluation for Eye Dryness-II, and biomarkers will be assessed throughout the trial. Safety will be assessed based on adverse events, vital signs, laboratory tests, visual acuity, and intraocular pressure. **Discussion:** Our study results are expected to provide clinical evidence for the use of DED as an effective and safe agent for DED.

## 1. Introduction

Dry eye disease (DED) is a “multifactorial disease of the tear film and ocular surface that results in discomfort, visual disturbance, and tear film instability, with potential damage to the ocular surface. It is accompanied by an increased osmolarity of the tear film and subacute inflammation of the ocular surface”, as proposed by the Tear Film and Ocular Surface Dry Eye Workshop II [1]. Contrary to the previous definition of DED, it focuses more on its pathogenesis, including tear hyperosmolarity, inflammation, neurosensory abnormalities, and unstable tear films [2], while ocular inflammation is believed to play a central role in the pathogenesis of DED [3,4].

Symptoms of dry eye vary in severity and include ocular discomfort, pain, fatigue, foreign body sensation, burning, and visual disturbances [5]. DED leads to significant impairment of quality of life, including aspects of physical, social, and psychological function, such as depression and anxiety disorders [6,7]. DED affects approximately 10.8–57.4% of the population worldwide [8,9], accounting for one of the most common diseases causing patients to visit ophthalmology clinics [10]. The prevalence of DED increases with age; however, it has also recently increased among young people with modern lifestyles and digital environments, including the intensive use of computers or smartphones, the use of contact lenses, and higher psychological stress [11,12]. Therefore, the impact of DED on public health has become more important, and the economic burden of DED on affected patients is more significant. The annual direct cost per patient is estimated to be USD 783 in the United States, USD 664 in Europe, and USD 530 in Japan [13].

The treatment of DED depends on the disease’s severity and etiology. Artificial tears are widely used as the first-line treatment, with patient education and environmental control. When insufficient, anti-inflammatory therapy (topical corticosteroids or topical Cyclosporine A), oral supplements (essential fatty acids), and gels/ointments are administered. Other options include autologous serum, oral tetracycline, punctual plug/occlusion, contact lenses or goggles, systemic anti-inflammatory medications, and surgery when previous treatment is inadequate [5,14,15]. Artificial tears only relieve symptoms in the short term, without resolving the disease process and causes. Topical cyclosporine A or corticosteroids target inflammatory pathways; however, some ocular side effects, such as temporary redness or burning, make them intolerable for long-term use [16,17]. Autologous serum poses a risk of anemia and blood-borne infection [18] and punctual plugs pose a risk of secondary infection [19]. Over time, sophisticated multiple-action combination formulations have gradually replaced simple water-adding medications. They are molecules or combinations of molecules that can improve the quality and quantity of the tear film components but have limited capabilities to interact with the ocular surface epithelia [20].

Owing to these limitations in DED treatment, an effective and safe treatment is needed. Recently, various options to manage the inflammatory pathways of DED have increased dramatically, and dietary modifications, such as essential fatty acids and complementary medicines, have been proposed as promising candidates for the treatment of DED [15]. In East-Asian countries, USL, the extract of Achyranthis Radix (AR), has been used as an herbal medicine for treating arthritis, osteoporosis, delayed menses, and edema [21,22]. AR is also approved as a functional food by the Ministry of Food and Drug Safety in Korea for its effect on maintaining healthy joints and cartilage. Previous pharmacological studies of AR have revealed its anti-inflammatory efficacy via heme oxygenase-1 induction and nuclear factor-κB suppression in macrophages [23], as well as its antibacterial [24], anti-oxidant [25], and anti-platelet activities [26]. Based on the strong anti-inflammatory properties of AR, we administered AR to patients with DED, anticipating that it may also be effective against ocular surface inflammation. A previous experimental study revealed that AR protected against DED by inducing tear secretion and improving corneal irregularity in a particulate matter-induced DED rat model [27]. The bioactive phytochemicals of AR have been reported to be triterpenoids, polysaccharides, and phytoecdysteroids; we analyzed the major components of USL using high-performance liquid chromatography (HPLC) [28]. In addition, we found that AR does not induce oral toxicity or genotoxicity in in vivo and in vitro testing [29].

In this study, we aimed to explore the efficacy and safety of USL in patients with DED and determine the appropriate dosage of USL required for DED treatment. We planned a randomized, double-blind, placebo-controlled, parallel, phase 2 clinical trial of two different doses of USL compared with placebo. We will measure both objective and subjective outcomes associated with DED and observe anti-inflammatory biomarkers to understand the pathways of USL that show efficacy.

## 2. Method and Analysis

### 2.1. Trial Design

This study is a phase 2, dose-finding, double-blind, randomized placebo-controlled trial to evaluate the efficacy and safety of two different doses of USL, compared with a placebo, for DED treatment. The trial will be conducted at Daejeon University Daejeon Korean Medicine Hospital and is set to start recruitment in January 2025. Participants who sign a written informed consent form after receiving a comprehensive explanation of the trial will be screened, and 120 participants will be enrolled after the eligibility assessment. Eligible subjects will be randomized into three groups in a 1:1:1 allocation ratio: standard-dose USL (1 g/day), high-dose USL (2 g/day), and placebo groups. The subjects would be asked to administer one of the medications twice a day for 12 weeks and visit five times (at screening, baseline, week 6, week 12, and week 14) to evaluate the efficacy and safety outcomes (Figure 1, Table 1). This study follows the guidelines of the Standard Protocol Items: Recommendations for Interventional Trials (SPIRIT) [30] and will be conducted in compliance with ethical principles in the Declaration of Helsinki and Good Clinical Practice guidelines [31].

This study protocol was approved by the Institutional Review Board of Daejeon University Daejeon Korean Medicine Hospital (DJDSKH-23-DR-11), and registered at Clinicaltrials.gov (NCT06016010).

### 2.2. Participants

#### 2.2.1. Inclusion Criteria

Participants who meet the following criteria will be enrolled in this trial: (1) subjects aged over 19 years; (2) subjects with dry eye symptoms (stiffness, foreign body sensation, irritation, bloodshot eyes, itching, blurred vision, pain, etc.) for at least 3 months; (3) subjects who have had both eyes screened, with a corrected visual acuity of 0.2 or more; (4) subjects with a fluorescein corneal staining score (Oxford grading) ≥ 2, tear break-up time (TBUT) ≤ 10, and Schirmer’s test ≤ 10 mm at screening; (5) subjects with an Ocular Surface Disease Index (OSDI) ≥ 23 at screening; and (6) subjects who voluntarily agree and provide written informed consent to participate in the clinical trial.

#### 2.2.2. Exclusion Criteria

The exclusion criteria [32,33] include (1) current or history of ocular disorders (ocular surgery, diseases, and trauma) within 2 months before the study that may affect the study results. These include abnormal eyelid function, such as disorders of the eyelids or eyelashes; ocular allergies or current treatment for allergic diseases of the eye (antihistamine, topical ocular mast cell stabilizer use, etc.); and cicatricial keratoconjunctivitis caused by pterygium, pinguecula, herpetic keratopathy, conjunctival scarring (cicatricial pemphigoid, Steven–Johnson syndrome and alkali damage), neurogenic keratitis, lack of congenital lacrimal gland, corneal transplantation or keratoconus; (2) acute eye inflammation/infection within 3 months before the study; (3) subjects who have undergone eye surgery (including LASIK/LASEK) within 12 months before the study; (4) those who have undergone lacrimal punctal occlusion, cauterization of the punctum, or an intense pulsed light procedure within 3 months before the study; (5) wearing contact lenses within 72 h of screening or planning to wear contact lenses during the study period; (6) intraocular pressure (IOP) > 22 mmHg on more than one side; (7) autoimmune diseases (e.g., Sjögren’s syndrome, Graves’ disease, systemic lupus erythematosus, and rheumatoid arthritis); (8) use of cyclosporine or diquafosol in any form (systemic or topical) within 1 month before the study; (9) current or history of medical conditions (glaucoma, ocular allergy, ocular inflammation/infectious disease, etc.) within 1 month of proposed treatment with topical agents besides artificial tears; (10) those who have taken or are taking steroid drugs or immunosuppressants (azathioprine, tacrolimus, cyclosporine, mycophenolate mofetil, etc.) that may affect immune function within 3 months prior to screening; (11) those who have taken antihypertensive drugs, such as antihistamines and beta-blockers, antidepressants and diuretics that can worsen dry eye; (12) severe abnormal liver function (aspartate transaminase or alanine transaminase values ≥ 2 times the upper limit of normal) and abnormal renal function test results (creatinine values ≥ 2 times the upper limit of normal); (13) genetic disorders, such as glucose–galactose malabsorption, Lapp lactase deficiency, and galactose intolerance; (14) comorbidities that may interrupt the treatment or assessment (cancer and disorders of the liver, kidney, cardiovascular system, psychiatric system, endocrine system, respiratory system, and central nervous system; (15) unregulated hypertension (high blood pressure of 160 mmHg in the condenser or >100 mmHg during relaxation); (16) unregulated diabetes (fasting blood sugar exceeding 180 mg/dL); (17) hepatitis A, hepatitis B, or hepatitis C; (18) history of hypersensitivity reaction to the active ingredients of the investigational medicine; (19) history of excessive alcohol use or drug addiction; (20) pregnancy or lactation; (21) those who did not agree to use medically permitted methods of contraception; (22) those who had participated in other clinical trials within the last 4 weeks; and (23) subjects who are judged as ineligible to participate in this study.

#### 2.2.3. Sample Size

The estimated sample size required for this trial is 120 patients (40 patients per group), based on previous comparable studies [34,35,36]. Although we could not calculate the sample size based on the exact effect size, as our study is the first trial using USL on patients with DED, we calculated the sample size based on previous studies expected to have similar effects. We assumed the difference in the changes in TBUT as 1.3, and the standard deviation (SD) as 1.8 from baseline to post-intervention between the control and standard-dose USL groups. The power to detect differences is assumed to be 0.8, with the two-sided significance level set at 0.05. The ratio of the allocation of subjects between groups is 1:1:1, and the dropout rate is assumed to be 0.2.

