### 2.7. Statistical Analysis

Statistical analyses of all outcomes will be conducted by an independent statistician using SAS Version 9.4 Analytics Pro software. Continuous variables will be presented as the mean ± SD and categorical variables will be presented as frequencies and percentages. For efficacy analysis, a full analysis set (FAS) based on intention-to-treat (ITT) analysis will be performed as the primary analysis, and PP analysis will be used for secondary analysis. All randomized participants who are evaluated at least once after administration of the trial medication will be included in the FAS, and only those who complete the trial without violating the protocol will be included in the PP set. A safety analysis will be conducted for all participants who are randomized and administered the trial medication at least once.

The primary and secondary efficacy outcomes will be analyzed using the mixed-effects model for repeated measures, with each group and visit set as fixed effects and participants as random effects. In addition, the difference between pre- and post-treatment within groups will be analyzed using Student’s paired *t*-test or Wilcoxon signed-range test, depending on normality. A multiple imputation method will be used for missing values. The efficacy of USL will be accepted at a significance level of 2.5% in both TBUT and OSDI compared with the placebo, whereas other secondary outcomes will be accepted at a 5% significance level.

To analyze safety outcomes, Fisher’s exact test will be used to compare the number of AEs between the groups, and Student’s paired *t*-test or the Wilcoxon signed-rank test will be performed to analyze the differences between pre- and post-treatment laboratory variables, vital signs, visual acuity, and IOP. Demographic characteristics will be analyzed using the Wilcoxon rank-sum test or independent *t*-test for continuous variables and Fisher’s exact test or the chi-square test for categorical variables.

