## 3. Discussion

Despite the growing burden of DED on public health, current treatments for DED present unmet medical needs owing to their side effects or ineffectiveness. Clinicians and patients with DED seek better treatment therapies to manage inflammation and ocular symptoms; nutritional supplements or complementary medicine have emerged as promising candidates for DED by managing ocular surface inflammation [51]. As inflammation is recognized as a major factor in the pathogenesis of DED, we anticipate that the anti-inflammatory effects of USL would improve the symptoms and signs of DED.

Our trial was designed to evaluate the efficacy and safety of USL for DED compared with a placebo and to determine the appropriate dosage of USL. We plan to conduct a phase 2, double-blind, dose-finding, randomized placebo-controlled trial, and both objective signs and subjective symptoms of DED, as well as cytokines related to inflammation, will be investigated. Objective signs and subjective symptoms are important in the diagnosis and management of DED; however, previous studies have reported a lack of association between them, making DED more complicated. The Food and Drug Administration (FDA) recommends that the efficacy of treatment should be demonstrated by showing significant differences in objective prespecified signs and subjective prespecified symptoms of dry eye. Moreover, the FDA suggests that different endpoints for objective signs (conjunctival staining, corneal staining, Schirmer’s test score, and TBUT) or subjective symptoms should be conducted when designing clinical trials for the treatment of DED. According to the FDA guidelines, we will evaluate TBUT and OSDI as primary outcomes and other objective endpoints, including fluorescein corneal staining score, Schirmer’s test, meibomian gland test, and subjective endpoints of VAS and SPEED-II as secondary outcomes. In addition, to investigate the inflammatory effects of USL, cytokines IL-1β, IFN-γ, and TNF-α will be measured.

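### The stated 80% power is for TBUT alone at a two-sided 5% level; the plan accepts efficacy at 2.5% in both TBUT and OSDI, and the two statements are not reconciled

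*Protocol article*

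**What the plan says.** Section 2.2.3 (Sample Size) bases 120 patients, 40 per group, on TBUT: "We assumed the difference in the changes in TBUT as 1.3, and the standard deviation (SD) as 1.8". The contrast is "between the control and standard-dose USL groups". The error rates are given as: "The power to detect differences is assumed to be 0.8, with the two-sided significance level set at 0.05". The remaining inputs are: "The ratio of the allocation of subjects between groups is 1:1:1, and the dropout rate is assumed to be 0.2". OSDI does not enter the calculation.

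Section 2.6.1 names two primary outcomes, TBUT for signs and OSDI for symptoms, each as change from screening to week 12. Section 2.7 (Statistical Analysis) gives the decision rule: "The efficacy of USL will be accepted at a significance level of 2.5% in both TBUT and OSDI compared with the placebo". The same sentence puts secondary outcomes at 5%. It does not say whether the 2.5% is one- or two-sided, or whether it allows for two endpoints or for two doses.

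The Discussion links the choice of endpoints to a regulatory recommendation that "efficacy of treatment should be demonstrated by showing significant differences in objective prespecified signs and subjective prespecified symptoms of dry eye". It also notes, on signs and symptoms, that "previous studies have reported a lack of association between them".

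**The concern.** The level used to size the trial (two-sided 5%, one endpoint) is not the level used to decide it (2.5%, two endpoints). Taken at its word, Section 2.7 sets a stricter test on TBUT than the one that was powered, and adds OSDI, for which the calculation makes no allowance. A reader who sees 0.8 will take it as the chance of a positive trial if the assumed effect is real. Under the stated rule that chance is lower.

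This matters in a dose-finding trial because a negative result may be read as evidence against the product or against one dose, when a fair part of the explanation could be low power. The Discussion relies on the number enrolled being large enough to show treatment differences.

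**Working it through.** **Inputs.** From Section 2.2.3: difference 1.3, SD 1.8, power 0.8, two-sided 5%, dropout 0.2, 40 per group. From Section 2.7: level 2.5%. The documents give no OSDI effect and no TBUT–OSDI correlation, so both are varied below as assumptions.

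**1. Reproduce the plan's figure.** Standardised effect = 1.3/1.8 = 0.722.
- Normal approximation: n = 2(1.960 + 0.842)²/0.722² = 30.1, so 31 per group; 31/0.8 = 38.75, so 39.
- Two-sample t-test (noncentral t): 32 per group; 32/0.8 = 40, the stated number.
- A one-sided 5% test would need 24, or 30 after dropout, which does not match.

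So 40 per group is correct for TBUT, standard dose versus placebo, at two-sided 5%.

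**2. TBUT power at each level.** With n per group the noncentrality is 0.722 × √(n/2), which is 2.889 at n = 32 and 3.230 at n = 40. The normal approximation to power is Φ(noncentrality − z), with z = 1.960 at 5% and 2.241 at 2.5%.

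| Evaluable per group | Two-sided 5%: t (normal) | Two-sided 2.5%: t (normal) |
|---|---|---|
| 32 (20% lost) | 81.2% (82.4%) | 72.2% (74.1%) |
| 40 (nothing lost) | 89.1% (89.8%) | 82.5% (83.9%) |

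At two-sided 2.5%, 80% power on TBUT needs 38 evaluable by the t-test; 38/0.8 = 47.5, so 48 randomised per group, or 144 in all. The normal approximation gives 37, then 47, or 141 in all. A one-sided 2.5% test is the same as two-sided 5% in the favourable direction, so the 5% column then applies.

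**3. Power to meet both endpoints, 32 evaluable per group.** The probability of meeting both cannot exceed the smaller of the two single-endpoint powers. With t-based single-endpoint powers p₁ and p₂, joint power is the bivariate normal probability Φ₂(Φ⁻¹(p₁), Φ⁻¹(p₂); ρ).

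| Assumed OSDI effect (SD units) | Two-sided 2.5%, ρ = 0 / 0.3 / 0.5 / 0.8 | Two-sided 5% (= one-sided 2.5%), same ρ |
|---|---|---|
| 0.722 (equal to TBUT) | 52 / 56 / 58 / 64% | 66 / 68 / 70 / 74% |
| 0.5 | 28 / 32 / 34 / 38% | 41 / 44 / 46 / 50% |
| 1.0 | 69 / 70 / 71 / 72% | 79 / 80 / 80 / 81% |

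Using normal-approximation powers instead raises the equal-effect row at 2.5% to 55–66%. The Discussion's remark on weak association between signs and symptoms points to the low-correlation end.

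**The case against.** **The calculation is not wrong.** A reader might infer an arithmetic error in Section 2.2.3. There is none: the figure reproduces, and the section says which endpoint, contrast and level it refers to. The defect is that this level is not the one used for the decision. This stands.

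**The 2.5% may be one-sided.** Section 2.7 does not exclude it, and TBUT power would then be about 81%. Setting secondary outcomes at 5% in the same sentence makes a stricter level on the same scale the more natural reading, but the text is ambiguous. A flat cap of 72% on the chance of success is therefore not supported; it holds only for a two-sided 2.5% with 32 evaluable per group. Even on the one-sided reading, joint power at an equal OSDI effect is 66–74%.

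**Dropouts are not all lost.** The primary set keeps anyone with one post-dose evaluation, and the analysis is a repeated-measures mixed model with multiple imputation. Some information from dropouts will be retained, so TBUT power at two-sided 2.5% lies between 72% and 82.5%. But the upper end assumes no loss at all, whereas Section 2.2.3 plans for 20% and claims no gain from the model.

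**Either endpoint may suffice.** If each were tested at 2.5% and one were enough, power for at least one would be about 81–92% at an equal OSDI effect (correlation 0.8 to 0). The wording of Section 2.7 and the recommendation cited in the Discussion both favour requiring the pair. TBUT alone would still have about 72% at two-sided 2.5%.

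**OSDI planning values may be in the full protocol.** This is fair for a condensed article, so their absence is not itself the point. What the article does state is an 80% that does not apply to the rule it also states.

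**This is a phase 2 trial.** The Discussion admits that the effect size is borrowed and promises later studies with an accurately calculated size. That acknowledges uncertainty about the effect; it does not explain the use of two significance levels.

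**Conclusion.** The concern holds in this form: the 0.8 in Section 2.2.3 applies to TBUT, standard dose versus placebo, at two-sided 5%, and not to the decision rule in Section 2.7.

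The drop from about 81% to about 72% for TBUT follows from the document's own inputs, given a two-sided 2.5% and 32 evaluable per group. If both endpoints are required, the further loss depends on OSDI values that the documents do not give. At an equal standardised effect, joint power per dose falls short of 80% on either reading of the 2.5%. It comes close to 80% only if the 2.5% is one-sided and the OSDI effect is clearly larger than that assumed for TBUT. The joint figures show the range under assumptions; they are not estimates for this trial.

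**What to change.** 1. In Section 2.7, state whether the 2.5% is one- or two-sided, whether it adjusts for the two endpoints or the two doses, and that both endpoints must be met (if that is the intention).
2. In Section 2.2.3, restate the power at that level and rule. If it is two-sided 2.5%, this is about 72% for TBUT with 32 evaluable per group.
3. Give both-endpoint power as a range, with the assumed OSDI difference, SD and correlation stated.

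The cost is wording in two paragraphs and a less favourable power statement. No extra patients are needed for these corrections.

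Optional, as a design choice: if both endpoints are required for a given dose, no split of alpha between them is needed, and each can be tested at the full level. Testing the two doses in a prespecified fixed sequence at two-sided 5% then controls the error across doses and restores about 81% TBUT power for the first-tested dose, if the assumed difference holds for it. A reader might expect Holm across doses to do the same, but its first step is still at 2.5%, so it recovers power only in part. Under either procedure joint power at an equal OSDI effect stays below 80% with 32 evaluable per group (66–74% for the first dose in a fixed sequence), so it should be disclosed in any case.
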